## Methods

### Design of the study

This randomised controlled trial will used 2 arms parallel groups design. The intervention group will benefit from an early specialized palliative care intervention in addition to standard care. The control group will benefit from standard care. Consenting participants will be randomly allocated to one of the groups after baseline assessment. Patients will continue to have the same access to specialized medical services as available to them prior to entry into the trial.

### Setting

The study will be conducted in the largest tertiary university hospital in Switzerland. Potentially eligible patients will be identified during their attendance at the ambulatory consultation of the Division of Pulmonary Disease and/or during their hospitalization in the Division of General Internal Medicine at Geneva University Hospital.

The Division of Pulmonary Disease provides follow-up care for LTOT and/or NIV for an important proportion of COPD in Geneva. Furthermore it is the only public hospital in the Geneva area and most of the patients with COPD are admitted to the Division of General Internal Medicine if they present an acute exacerbation.

The area has a palliative care network with a community palliative care unit, involved in the project. Very few patients with COPD are addressed to this unit.

### Inclusion and exclusion criteria

The inclusion criteria are:

COPD defined according to GOLD criteria (FEV_1_/FVC <70%) stage III or IV (FEV_1_ < 50% predicted)
[36]

– and/or long term treatment with either domiciliary oxygen
[37] or home mechanical ventilation
[5]

– and/or one or more hospital admissions in the previous year for an acute exacerbation

The exclusion criteria are:

– Patients in their last days of life ( patient bedbound and/or semi comatose and/or take only fluid and/or no longer able to take oral drugs)

– Patients with cognitive impairment: Mini Mental status Examination ≤23 at the day of inclusion of patients
[38]

– Patients with active cancer

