The primary objective of the study is to assess the effectiveness of the introduction of early specialized palliative care on hospital, intensive care unit and emergency admissions of patients with severe and very severe COPD.

The secondary objectives are to assess impact of early palliative care on:

1. mood and anxiety of patients with severe and very severe COPD

2. health-related quality of life of patients with severe and very severe COPD.

3. pattern of antibiotics used during the last month of life

4. advance care planning and end-of-life decision-making

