### Control group

Patients randomized to the control group, i.e. who receive standard care alone, will not meet with the palliative support team unless the patient himself, his family or his treating physician request a meeting. These patients will remain in the control group, as this is already part of present practice.

Patients who present acute exacerbations will be treated by the participant’s GP or pulmonologist or by the emergency division according to usual practices and recommendations of our institution.

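### Patients already followed by specialist palliative care can be randomised in a trial of its introduction; the contrast between arms is reduced in these few patients, and a one-line exclusion would prevent this at little cost

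*Protocol article*

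**What the plan says.** All references are to the protocol article.

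- **Background (objectives).** The primary objective is "to assess the effectiveness of the introduction of early specialized palliative care on hospital, intensive care unit and emergency admissions".
- **Inclusion and exclusion criteria.** There are three exclusions. The first reads "Patients in their last days of life ( patient bedbound and/or semi comatose and/or take only fluid and/or no longer able to take oral drugs". The second is a low score on a cognitive test (MMSE of 23 or less), and the third is a current malignancy. Neither these nor the inclusion criteria mention palliative care. Recruitment procedure and Randomisation-allocation concealment add no screen for it.
- **Setting.** The area has a community palliative care unit that takes part in the project. Of this unit the article says "Very few patients with COPD are addressed to this unit".
- **Intervention.** The trial nurse belongs to the hospital's community palliative care unit, on a natural reading the same one. The first visit is within three weeks and lasts about an hour and a half. Visits then follow at least monthly for one year.
- **Design of the study.** "Patients will continue to have the same access to specialized medical services as available to them prior to entry into the trial".
- **Control group.** Control patients "will not meet with the palliative support team unless the patient himself, his family or his treating physician request a meeting", and those who do so remain in the control group.
- **Outcomes measures and Data collection.** Secondary outcomes, including advance directives, are collected at baseline. Health professionals involved over the past three months are also recorded. The examples given are nurses, dietician and occupational therapist; palliative care is not named.

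**The concern.** The trial asks what happens when specialist palliative care is introduced early. For a patient who already has it, the service is not being introduced, and the answer to the trial's question is not well defined. If that patient is allocated to control, the Design section keeps existing access open. The Control group section deals with requests for a meeting and does not say what happens to follow-up already in place. The difference in care between the arms is then smaller than the one the trial was sized to detect.

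The effect is dilution: the estimated differences in admissions, mood and advance care planning are pulled towards zero. Some of these patients may also enter with advance directives or a surrogate decision maker already in place, which leaves less room for change on that outcome.

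This is separate from control patients who ask for palliative care after randomisation. That is part of present practice and belongs in the intention-to-treat comparison. Existing palliative care is known before randomisation, so excluding on it introduces no bias between the arms.

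**Working it through.** **Inputs**
- From Power calculation: 80 per group, 80% power, two-sided alpha 0.05, a difference of 20% in hospital admissions. Between one third and one half of the patients followed for NIV or long-term oxygen are hospitalised at least once a year.
- From the abstract: 90 per group.
- From Background: among Canadian patients who died with COPD, 2.8% used palliative care at home and 5.1% in acute care hospitals. These are the only frequencies in the document. They are borrowed here as the assumed share *f* of enrolled patients already under palliative care.

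**Step 1: reproduce the stated sample size.** Read 20% as absolute points and use

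n = [1.96·√(2p̄(1−p̄)) + 0.842·√(p₁(1−p₁) + p₂(1−p₂))]² / (p₁−p₂)²

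with p̄ the mean of p₁ and p₂. For 0.39 against 0.19 this gives 80 per group; for 0.40 against 0.20 it gives 82. Over the stated range, 0.333 against 0.133 gives 70 and 0.50 against 0.30 gives 93. The figure of 80 therefore reproduces, but only at a control rate that the article does not fix. A relative reduction of 20% would need 388 to 741 per group and does not reproduce.

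**Step 2: dilution with zero contrast.** Suppose a share *f* has no contrast at all. This is the limiting case at that share.

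Observed difference = 20 × (1 − f):
- f = 0.028: 20 × 0.972 = 19.4 points
- f = 0.051: 20 × 0.949 = 19.0 points

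Approximate inflation of the sample size = 1/(1 − f)²:
- f = 0.028: 1/0.972² = 1.06
- f = 0.051: 1/0.949² = 1.11

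**Step 3: power.** Take 0.40 against 0.20 in the other patients and put the diluting patients at 0.20 in both arms. The control rate becomes (1 − f) × 0.40 + f × 0.20.

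| f | Control rate | Difference | n per group for 80% power | Power at 80 per group | Power at 90 per group |
|---|---|---|---|---|---|
| 0 | 0.400 | 0.200 | 82 | 79.4% | 83.9% |
| 2.8% | 0.394 | 0.194 | 86 | 77.3% | 82.0% |
| 5.1% | 0.390 | 0.190 | 90 | 75.4% | 80.3% |

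The loss at 80 per group is 79.4 − 77.3 = 2.1 points and 79.4 − 75.4 = 4.0 points.

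**Step 4: sensitivity.**
- Base control rate of one third: power at 80 per group goes from 85.6% to 83.8% and 82.2% (losses of 1.8 and 3.4 points).
- Base control rate of one half: from 73.7% to 71.4% and 69.3% (losses of 2.3 and 4.4 points).
- Diluting patients at the control rate of 0.40 in both arms instead of 0.20: 76.8% and 74.6% (losses of 2.6 and 4.8 points).

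The size of the loss is stable at roughly 2 to 5 points.

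**Step 5: number of patients.** With 160 patients in total, 0.028 × 160 ≈ 4 and 0.051 × 160 ≈ 8.

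**The case against.** The strongest reply is that this is a legitimate pragmatic design. The comparison is usual care, with occasional palliative contact, against usual care plus a defined programme, and the Control group section accepts such contact openly. That defence stands for contact that begins after randomisation. It is weaker for care already in place, because the stated objective is about introduction.

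A reader might infer that these patients have no contrast at all. The documents do not support that. An intervention patient already known to the unit would still be assigned the long first visit, visits at least monthly and a written plan to the treating physician. Nothing says that existing follow-up provides the same. Nor do the Design and Control group sections guarantee that palliative follow-up continues in a control; they leave access open. The contrast is reduced by an unknown amount.

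A reader might also infer a material loss of power. The Setting section speaks against it. The Canadian figures describe patients who died, whereas this trial excludes patients in their last days, so they may well overstate the share. A loss of about 8 points needs 10% of patients with zero contrast (71.2% power at 80 per group), and the article gives no support for such a share.

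Baseline collection of advance directives also helps: it shows who enters with that outcome met, although it does not restore the contrast.

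Finally, the article may condense a fuller protocol. It does, however, print the list as the exclusion criteria. If the full protocol already contains this exclusion, the point falls away.

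**Conclusion.** The gap is real and minor. As printed, the criteria let patients already under specialist palliative care be randomised in a trial of its introduction, and the contrast in those patients is reduced. The effect is dilution towards no difference. At assumed shares of 2.8% to 5.1% with zero contrast, the difference shrinks from 20 to between 19.4 and 19.0 points and power at 80 per group falls by about 2 to 4 points, or just under 5 under the less favourable assumption in Step 4. At 90 per group, power in the main illustration stays above 80%.

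These results rest on three assumptions: the borrowed shares, an absolute reading of the 20% difference, and a control rate near 0.40. Zero contrast makes them a ceiling at each share. The case for acting is that the change is cheap and brings the population into line with the stated question, not that the trial is seriously underpowered for this reason.

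**What to change.** Add one exclusion to Inclusion and exclusion criteria: *currently followed by a specialised palliative care team or the community palliative care unit*. Check it at the baseline appointment, after written consent and before randomisation, by asking the patient and consulting the records of the unit, which already takes part in the project.

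Limit it to current follow-up. A look-back window would be arbitrary and would remove patients with a single past contact, in whom the contrast is nearly full.

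Keep patients already randomised in the intention-to-treat analysis, and record for each whether specialist palliative care was in place at baseline. Naming it in the baseline item on health professionals would do this. Leave the Control group section as it is.

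The cost is a small number of candidates who become ineligible, a brief records check, and a minor eligibility amendment with ethics notification, because recruitment began in September 2013. The population before and after the amendment will differ slightly; the added baseline item lets this be described.

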### Recruitment procedure

Potential participants will receive information from our research nurse and will be advised as to what is involved if participating in the trial. Potential trial participants will be informed that they have a 50% chance of being allocated to the intervention group and a 50% chance to receive standard care. Reasons for declining to participate will be recorded as: not interested, too busy, don’t believe in it, declined randomisation, other. Other reasons for leaving the study prior to randomisation will be noted.

The study nurse will arrange an appointment for the baseline assessment with the patient. This first appointment will take place in the patient’s home or at the hospital, according to patient’s choice. At this appointment, written informed consent for participation in the study will be obtained from participants.

### Randomisation-allocation concealment

After giving written informed consent and filling in baseline measures, the patients will be randomly assigned to the "early palliative care" group or the "standard care only" group using sealed envelopes prepared using a computer program by [name] co investigator not involved in the inclusion of the patients, in a 1:1 ratio without stratification and with randomized block sizes ranging from 4 to 6.

### Ethics approval

The Ethics Commission of the University Hospital Geneva approval has been obtained prior to recruitment. All patients will provide written informed consent. Recruitment started in September 2013.

### Intervention

The theoretical basis of the intervention was established by reviewing the published literature on the impact of the early introduction of palliative care in patients with severe diseases
[7,8,12,14,16-18,22,24,32-34,39-49]. Information gathered in this phase has been used to develop the optimal intervention by a multidisciplinary group and a study design adapted to our regional health system. Researchers involved in the recruitment of the patients are blinded to the details of the intervention. Our team also established contacts with experts who had already developed specialized palliative care interventions in this type of population.

Patients assigned to the early palliative care group will meet a nurse attached to the community ambulatory palliative care unit of the HUG (USPC) within three weeks of inclusion and at least monthly thereafter during one year after inclusion. This nurse has a long experience in palliative care. The first consultation will take place at the patient’s home, unless the patient prefers to have the consultation at the pulmonary division. It will take approximately 1 h ½ to assess and discuss the different items. The subsequent monthly consultations will last approximately 30 minutes according to the needs of the patients. A consultation with a specialized palliative care physician or another specialist (psychiatrist, pulmonologist….) will be organized if intensity of pain, dyspnea, mood, anxiety and appetite disturbances are >4/10 on visual analogic scales (VAS) and both the patient and his/her physician agree. The individualised palliative care assessment and treatment plan will be forwarded in writing to the physician in charge of the patient within 24 hours of the consultation. These consultations will be at charge of the insurance of the patient. Details of the palliative consultation are described in Table 
1. We decided to establish a set of core interventions, but not to schedule these different items to respect the rhythm and needs of the patients. At the end of each consultation, the items discussed during the consultations will be collected. Participants who refuse to attend one or more palliative care interventions will be contacted by phone by the palliative care nurse to understand their reasons. If the patient, agrees a new appointment will be fixed.

**Table 1 T1:** Description of the palliative care intervention

1.	**Symptom management**
	- Assessment of symptoms with the Edmonton Symptom Assessment Scale
	- If intensity of pain, dyspnea, mood, anxiety and appetite >4 and patient agrees: patients will be referred to home based specialist palliative care team or another specialist (dieticians, pulmonologist, psychiatrist…)
	- Symptom management will follow the palliative care guidelines of the University Hospital of Geneva.
	- Non pharmacological interventions such as relaxation will be promoted according to Booth [42]
2.	**Understanding of illness and coping with the disease:**
	**-** History of disease made with the patient
	**-** Experience of patient with breathlessness
	**-** Information about dyspnea and the disease (discussion and booklet)
	**-** Information about morphine if needed (discussion and booklet)
3.	**Anticipation**
	**-** Values of the patients (what is important for you)
	**-** Patient preferences for end-of-life care: hospitalization f.ex
	**-** Information about advance directives, nomination of surrogate decision maker (booklet and discussion)
4.	**Relatives support**
	**-** Identification of the most important relative
	**-** Assessment of their needs
	**-** Provision of available resources
5.	**Social support**
	**-** Assessment of needs (financial, administrative.)
	**-** Provision of available resources
6.	**Spiritual support**
	**-** Assessment of needs
	**-** Provision of avalables ressources
7.	**Coordination of the health professionals**
	**-** Listing of the health professionals involved in the situation
	**-** Discussion with them of goals of care

### Control group

Patients randomized to the control group, i.e. who receive standard care alone, will not meet with the palliative support team unless the patient himself, his family or his treating physician request a meeting. These patients will remain in the control group, as this is already part of present practice.

Patients who present acute exacerbations will be treated by the participant’s GP or pulmonologist or by the emergency division according to usual practices and recommendations of our institution.

### Outcomes measures

Regarding the primary outcome, Hospital, ICU and emergency admissions will be collected in both groups form the medical records once a month. Length of stay in the different divisions, type of divisions (i.e.: internal medicine, rehabilitation) and reasons for admissions will be collected.

Regarding the secondary outcomes of the study:

– Mood and anxiety of patients will be measured with the self-assessment instrument: the Hospital Anxiety and Depression Scale (HADS)
[50,51]

– Quality of life will be measured with the SF-36 short form: a self-assessment scale validated in this population, and the COPD Assessment Test (CAT): a short, simple instrument for quantifying the symptom burden of COPD in routine practice

– Use of antibiotics during the last three months will be recorded

– Completion of advance directives, documented preferences for resuscitation, or nomination of surrogate decision maker will also be recorded

The secondary outcomes will be collected at baseline and at weeks 12, 24, 36 and 48.

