### Data collection

Baseline data will be collected in each patient’s home by the study nurse. The timing of interventions and data collection has been designed to not be too burdensome in this population with a severe disease
[15].

The baseline characteristics of the participants that will be measured are:

– Socio-demographic items: age, sex, marital status, education, children, living condition

– Smoking habits, weight, height, co-morbidities measured by the CIRS
[52], activities of daily living
[53], artificial nutrition (enteral, parenteral), prescribed treatment

– health professionals who participated to their care over the past three months (ie: nurses , dietician, occupational therapist)

– Additional equipment such as electric bed, wheelchair

– Characteristics and management of COPD: pulmonary function tests, oxygen saturation, use of oxygenotherapy, use of NIV, pharmacological treatment, numbers of acute exacerbations, admissions to emergency room, intensive care unit and hospital over the past three months Location and date of death will be collected from the medical records

Most of these data will be collected during the collection of primary and secondary outcomes (at weeks 12, 24, 36 and 48).

Data will be collected in computer files and will be rendered anonymous, without any reference to initials. Only the principle investigator will have the key to the correspondence between patient reference number and identity. The CRF (case report form) will be collected using SecuTrial software with the support of the Clinical Research Center, Geneva University Hospitals ([name]). A clinical research fellow, allocated for this project will adapt the data base and enter the data in the SecuTrial software.

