### Power calculation

One hundred-thirteen patients are currently followed by the Division of Pulmonary Disease in the University Hospital Geneva because of treatment with NIV and/or LTOT. We know that between one third and one half of these patients are hospitalized at least once during the year. Furthermore approximately 200 COPD patients per year are admitted to the Emergency Division of our hospital. Even if only a third of these patients are included in the study, this would give us sufficient statistical power to validly analyze our primary outcomes. Regarding the primary outcome, we calculated that a sample size of 80 patients per group would be adequate with an 80% power to detect a difference in hospital admissions of 20% between both groups at an α significance level (2-sided test) of 0.05.

With regard to missing data, we will use the conservative approach of carrying the last observation forward for all missing data in the intention-to-treat analyses. Poisson or binomial negative regression models will be used to compare count data between the groups while adjusting for potential confounder. The trend in the evolution of the different scores will be assessed using mixed linear regression models.

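### The antibiotic objective concerns the last month of life, but the only antibiotic outcome covers three months and is collected at scheduled assessments, so objective and outcome do not match

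*Protocol article*

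**What the plan says.** The Protocol article describes antibiotic use in two places.

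- **Objective** (end of Background, third secondary objective): the "pattern of antibiotics used during the last month of life".
- **Outcome** (Outcomes measures): "Use of antibiotics during the last three months will be recorded". The same section gives the timing: "The secondary outcomes will be collected at baseline and at weeks 12, 24, 36 and 48".

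Three further statements bear on whether another data stream could supply the missing piece.

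- Data collection says of patients who die: "Location and date of death will be collected from the medical records". It names no other item to be taken from records at death.
- Data collection also uses a three-month window for care received, "health professionals who participated to their care over the past three months", as a look-back from the assessment.
- Outcomes measures describes a monthly record review, but for the primary outcome: "Hospital, ICU and emergency admissions will be collected in both groups form the medical records once a month". Length of stay, type of division and reason for admission are listed with it. Antibiotics are not.

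**The concern.** An objective counted back from death can be answered only with data tied to the date of death, in people who have died. The stated outcome has no such tie. A three-month window recorded at entry and then every 12 weeks reads naturally as a look-back from each assessment, and it applies to everyone in the trial.

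Antibiotic use near the end of life is one of four secondary objectives. If the outcome is analysed as written and reported against that objective, the result will be labelled as end-of-life antibiotic use while describing mostly other periods in patients who are mostly still alive. A later analysis plan can choose how to analyse the data, but it cannot by itself create a death-anchored variable that the data collection did not provide for.

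**Working it through.** The article gives no figure to reproduce here. The check has two parts: a comparison of the two definitions, and a calculation of how much of the last month the stated schedule would reach.

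**1. The two definitions side by side**

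| | Objective (Background) | Outcome (Outcomes measures) |
|---|---|---|
| Window | one month | three months |
| Counted back from | death | scheduled assessment (from the collection times) |
| Population | patients who die | all randomised patients |

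The anchor in the right-hand column is not written in the antibiotic line itself. It follows from the collection times given for all secondary outcomes. Could the line instead mean the last three months of life? That cannot be recorded at baseline, and it would still disagree with the one month in the objective.

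**2. Coverage of the last month under a visit look-back**

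Inputs:
- Visit spacing: 12 weeks × 7 = 84 days (Outcomes measures).
- Length of the last month: m = 30 days, varied from 28 to 31.
- Assumption, not in the article: the gap g from the last visit to death is uniform on 0 to 84 days.
- The three-month look-back is longer than m, so its far end never limits coverage.

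Days of the last month that precede the last visit, and so fall inside its look-back: max(0, m − g).

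- Mean days covered = m² / (2 × 84) = 900 / 168 = 5.4 days.
- Mean share covered = m / (2 × 84) = 30 / 168 = 17.9%.
- Deaths with none of the month covered = 1 − m/84 = 54/84 = 64.3%.
- Deaths with part of it covered = 30/84 = 35.7%.
- Deaths with all of it covered: only if death falls on the visit day (g = 0), so essentially none.

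Sensitivity:

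| m (days) | Mean share, deaths to week 48 | None covered, to week 48 | Mean share, deaths to day 365 | None covered, to day 365 |
|---|---|---|---|---|
| 28 | 16.7% | 66.7% | 19.2% | 61.6% |
| 30 | 17.9% | 64.3% | 20.6% | 59.1% |
| 31 | 18.5% | 63.1% | 21.3% | 58.1% |

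The week-48 columns are the closed form, and a simulation of one million deaths agreed with it. The day-365 columns come from the simulation.

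Partial coverage helps little. The days covered are always the earlier part of the month, never those closest to death. They also sit inside a three-month total that does not separate them from the preceding weeks.

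**The case against.** The strongest reply is that the article names no source for the antibiotic data. It calls the anxiety, depression and SF-36 quality-of-life instruments self-assessments, but says of antibiotics only that use will be recorded. Medical records are already consulted monthly for admissions, and also for place and date of death. If antibiotic use also came from records, the scheduled collection after a death could cover the months that contain it, and dated prescriptions linked to the date of death would answer the objective. A condensed article may leave such detail to the full protocol.

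This stands as far as it goes. A reader might infer that antibiotic use in the last month of life is never recorded, or that the trial can yield no valid data on it. The article supports neither statement. It is silent on the source, and even on a visit-only reading about a third of deaths have part of the month covered.

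Two other extensions also lack support.

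- A reader might expect the missing-data rule, "carrying the last observation forward for all missing data in the intention-to-treat analyses", to fill the end-of-life variable with an earlier three-month window. The article does not say so, and for an objective confined to patients who die, a visit after death is not plainly missing data.
- A reader might try to size the problem by the number of deaths. The article's two-year mortality of 36–50% follows admission for an acute exacerbation, whereas eligibility also admits patients without such an admission. A one-year figure would need a further assumption about how risk runs over time.

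The reply does not remove the mismatch. The article states both the objective and the outcome, they disagree, and nothing else in it reconciles them. Even with records as the source, a three-month total would contain the last month without isolating it.

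**Conclusion.** The point holds as an inconsistency between a stated objective and its stated outcome. They differ in window, anchor and population, and the collection as described does not isolate the last month of life. This part rests on the text alone.

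The size is illustrative. It assumes a look-back at 12-weekly visits and deaths spread evenly between them. On that basis the last visit covers about 18% of the final 30 days on average (17–21% over the variations tried), about 64% of deaths have none of the month covered (58–67%), and essentially none have all of it.

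One secondary objective is affected. The primary outcome and the sample size are not.

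**What to change.** Make the objective and the outcome the same quantity, by one of two routes.

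- **(a) Keep the end-of-life question.** Define the outcome as antibiotic use in the 30 days before the recorded date of death, taken from the medical records in the review that already yields place and date of death. Report it descriptively by arm among patients who died. That subset is formed after randomisation, so a difference between arms within it would not be a randomised comparison. The cost is one extra abstraction item per death.
- **(b) Keep the present collection.** Restate the third secondary objective as antibiotic use over each three-month period in all randomised patients. This needs only a change of wording, but it gives up the end-of-life question.

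Under either route, state the source of the antibiotic data and the set of patients analysed.
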